## 3 Statistical analysis

---

### 3.1 Statistical principles

#### **3.1.1 Reporting of results**

Results will be reported in accordance with the CONSORT extension for stepped wedge trials.[15]

#### **3.1.2 Level of statistical significance**

All applicable statistical tests will be 2-sided and will be performed using a 5% significance level. No adjustments for multiplicity will be made. Instead, 95% confidence intervals and p-values will be reported.

#### **3.1.3 Statistical software**

Stata v17 or later (StataCorp. Stata Statistical Software: Release 17. College Station, TX: StataCorp LLC), and R version 4.2.2 or later (The R Foundation for Statistical Computing) will be used.

### 3.2 Analysis populations

The primary analyses of primary and secondary outcomes will be conducted under the principle of intention-to-treat. When analysing patient-level outcome data or the survey data, patients will be assumed to have been exposed to the education intervention from the point in time at which their local government area was assigned to commence active implementation of that intervention with data from the transition periods excluded from analysis, regardless of whether the education campaign had commenced, or whether the patient was aware of the education campaign. When analysing data collected at the local government area level the local government area will be assumed to be in the education intervention from the point in time at which that local government area was assigned to actively implement the intervention, with data from the transition periods excluded from analysis.

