### **Australian campaigns**

The Heart Foundation has previously used public mass media advertisements to increase the Australian public's awareness of ACS symptoms and the need for an urgent response. Evaluations of such campaigns (e.g. the Warning Signs campaign), led by CIs/AIs, have shown significant success with associated improvements seen in the public's symptom knowledge, response to symptoms (timeliness and ambulance use) and in prehospital deaths.

However, mass media campaigns are expensive, not sustainable and the long-term gains are unknown. For example, the Warning Signs campaign cost an estimated \$16 million, ran intermittently between 2009 and 2013, and, as funding was reliant on donations and local government contributions, had variable exposure across the country. Just over half (55%) of Australians and two-thirds (64%) of ACS patients recalled seeing the advertising during the campaign period. The long-term effectiveness of this campaign is unknown, but available data from other campaigns suggest regular and sustained advertising is necessary. There are also concerns about the potential for increased use of emergency services by patients without ACS (i.e. the "worried well") as a result of such campaigns. Data from the Warning Signs campaign suggest this number may be significant. This is an important consideration as emergency services are finite resources, and attending to high numbers of non-ACS patients may well divert resources away from the people with medical emergencies.

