### *Education materials and resources*

Once an LGA crosses over into the intervention phase, a launch event will be held and the HM coordinator will start delivering community education (Table 2). This education will address each of the study's objectives using varying modes of delivery (e.g. in person\* and digital). Partner resources will be used (e.g. Heart Foundation's Heart Attack Action Plan – available in multiple languages and magnetic to keep on fridge). HM resources used by HM Coordinators (e.g. videos and presentations) will be developed from existing resources and tested with Partners and collaborators.

\* All education will be online (e.g. Zoom webinars) if Government restrictions apply due to the COVID pandemic.

*Table 2. Proposed methods of HM education.*

|                                                                                                                                                                                                                                                                                                                                                                                                                                                                                                                                                                                                                                                                                                                                                                                                                                                                                                                                                                                                                                                                                                                                                                                                                                                                                                                                                                                                                                                                                                                                                                           |

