### Allocation and sequence generation

Over the 16-month study period, the eight LGAs will move into the intervention phase at two month intervals. As four LGAs are in close proximity (Whittlesea-Hume; Greater Bendigo-Campaspe), these LGAs will switch from control to intervention periods at the same time to avoid possible contamination. For planning purposes, allocation and sequence generation has already been performed. Allocation of randomisation was performed blinded, by the CIA, study statistician and overseen by an independent investigator. This was performed by CIA allocating each LGA a study number from 1 to 8, which was then sent to the independent investigator. Following this the study statistician generating the randomisation sequence with the numbers 1 to 8, this information was then linked back to the LGA allocation numbers (Table 4).

*Table 4. Allocation and sequence generation.*

| LGAs        | Time Period |    |    |    |    |    |    |    |
|-------------|-------------|----|----|----|----|----|----|----|
|             | T1          | T2 | T3 | T4 | T5 | T6 | T7 | T8 |
| Bendigo     |             | X  |    |    |    |    |    |    |
| Campaspe    |             | X  |    |    |    |    |    |    |
| Maribyrnong |             |    | X  |    |    |    |    |    |
| Wodonga     |             |    |    | X  |    |    |    |    |
| Warrnambool |             |    |    |    | X  |    |    |    |
| Mildura     |             |    |    |    |    | X  |    |    |
| Whittlesea  |             |    |    |    |    |    | X  |    |
| Hume        |             |    |    |    |    |    | X  |    |

*X = Launch Event*

*T = time period, two months in duration*

*Proposed timeline for intervention. Light grey cells – control period; medium-grey cells- transition period; dark grey cells – intervention period.*

Statistical methods of analyses for the primary and secondary clinical outcomes

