### **Stepped wedge trial schematic**

The schematic for the Heart Matters stepped wedge trial is displayed below. It has 6 sequences, where 2 local government areas are assigned to each of the first and last sequences of the trial. Periods are each two months long, with transition periods between control and active implementation periods incorporated in each sequence.

Figure 1. Stepped wedge cluster trial design including baseline, transition, and active implementation periods.

[figure not shown]

LGA: Local Government Area

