## 5 Proposed outputs

### 5.1 Tables

**Table 1. Number of acute coronary syndrome patients arriving at emergency departments via EMS and total number of acute coronary syndrome patients arriving at emergency departments by LGA and period**

|       | Dec/Jan | Feb/Mar | Apr/May | Jun/Jul | Aug/Sep | Oct/Nov | Dec/Jan | Feb/Mar | Total   |
|-------|---------|---------|---------|---------|---------|---------|---------|---------|---------|
| LGA 1 | n/N (%) |         | n/N (%) | n/N (%) | n/N (%) | n/N (%) | n/N (%) | n/N (%) | n/N (%) |
| LGA 2 | n/N (%) |         | n/N (%) | n/N (%) | n/N (%) | n/N (%) | n/N (%) | n/N (%) | n/N (%) |
| LGA 3 | n/N (%) | n/N (%) |         | n/N (%) | n/N (%) | n/N (%) | n/N (%) | n/N (%) | n/N (%) |
| LGA 4 | n/N (%) | n/N (%) | n/N (%) |         | n/N (%) | n/N (%) | n/N (%) | n/N (%) | n/N (%) |
| LGA 5 | n/N (%) | n/N (%) | n/N (%) | n/N (%) |         | n/N (%) | n/N (%) | n/N (%) | n/N (%) |
| LGA 6 | n/N (%) | n/N (%) | n/N (%) | n/N (%) | n/N (%) |         | n/N (%) | n/N (%) | n/N (%) |
| LGA 7 | n/N (%) | n/N (%) | n/N (%) | n/N (%) | n/N (%) | n/N (%) |         | n/N (%) | n/N (%) |
| LGA 8 | n/N (%) | n/N (%) | n/N (%) | n/N (%) | n/N (%) | n/N (%) |         | n/N (%) | n/N (%) |
| Total | n/N (%) | n/N (%) | n/N (%) | n/N (%) | n/N (%) | n/N (%) | n/N (%) | n/N (%) | n/N (%) |

n=number of acute coronary syndrome patients arriving at emergency departments via EMS emergency medical services in that LGA in that period; N= total number of acute coronary syndrome patients arriving at emergency departments via emergency medical services EMS in that LGA in that period. Yellow cells = control periods; blue cells = Heart Matters intervention periods; black cells = transition periods. Data from transition periods will not be analysed.

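### The transition-period exclusion also covers the emergency-demand outcomes, so the planned analysis cannot speak to the launch months

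*Supplement*

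**What the plan says.** SAP section 3.2 sets one rule: "The primary analyses of primary and secondary outcomes will be conducted under the principle of intention-to-treat". For patient-level and survey data, exposure counts from when the LGA was due to "commence active implementation of that intervention with data from the transition periods excluded from analysis". A separate sentence applies the same rule to LGA-level data, with exposure running from when the LGA was "assigned to actively implement the intervention, with data from the transition periods excluded from analysis". The note to SAP Table 1 repeats it: "Data from transition periods will not be analysed". On the length of the excluded period, the SAP schematic text says: "Periods are each two months long, with transition periods between control and active implementation periods incorporated in each sequence".

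Sections 3.8.2 (chest pain calls, as a proportion of all calls) and 3.8.4 (ED presentations for unspecified chest pain and non-chest-pain calls, as rates) make no exception.

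On timing, the protocol's section on education materials says: "Once an LGA crosses over into the intervention phase, a launch event will be held and the HM coordinator will start delivering community education". Protocol Table 4 marks each LGA's launch cell with the key "X = Launch Event". The protocol background gives a reason to watch demand: "There are also concerns about the potential for increased use of emergency services by patients without ACS". Its secondary objectives ask whether ED presentations for ACS and unspecified chest pain, and ambulance calls, increase.

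**The concern.** Leaving out a build-up period is sensible for a benefit that takes time to develop, and the primary outcome was sized that way. Extra demand on emergency services is a different question, because it may begin with first exposure. The launch is meant to involve the partners, local health professionals and local media. If the months discarded are the launch months, a short rise in chest pain presentations or calls at launch never enters the analysis. A finding of no added burden would then describe only the time from the end of the transition, though readers may take it to cover the whole campaign.

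**Working it through.** **1. Is one period per LGA really excluded?** SAP section 2.8 gives 8 LGAs, 40 patients per LGA-period and a total of 2240. With eight periods less one transition, 8 × 7 × 40 = 2240, exactly the stated figure. Under a linear mixed-model approximation with fixed period effects and an exchangeable ICC of 0.09, the 56 remaining cells give an SE of 0.0383 with the variance taken at the mean proportion 0.665, or 0.0396 at 0.61. Power for 61% v 72% is then 0.82 or 0.79, which matches the stated 80%. The primary outcome was therefore planned with the exclusion built in.

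**2. Are the excluded cells the launch cells?**

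| LGA | Launch X, protocol Table 4 | Active periods after it |
|---|---|---|
| Bendigo | T2 | 6 |
| Campaspe | T2 | 6 |
| Maribyrnong | T3 | 5 |
| Wodonga | T4 | 4 |
| Warrnambool | T5 | 3 |
| Mildura | T6 | 2 |
| Whittlesea | T7 | 1 |
| Hume | T7 | 1 |

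The blank (transition) cells of SAP Table 1 follow the same pattern: T2, T2, T3, T4, T5, T6, T7, T7. SAP Table 8 runs to six periods on treatment, so the first sequence is counted from T3, after its launch period.

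**3. How much is left out?** Active cells: 6 + 6 + 5 + 4 + 3 + 2 + 1 + 1 = 28. Transition cells: 8. Share: 8 / (28 + 8) = 22%. For Whittlesea and Hume it is one of only two periods.

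Weighting by the residents in protocol Table 1, and assuming its LGA1 to LGA8 follow the order of names in SAP Table 2:
- transition resident-periods: 779,316
- active resident-periods: 6 × 149,862 + 5 × 86,942 + 4 × 40,100 + 3 × 33,655 + 2 × 54,658 + 1 × 414,099 = 2,118,662
- share: 779,316 / 2,897,978 = 27%

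Those residents total 779,316, whereas the protocol's consent section and SAP section 2.2 give 1.8 million for the same eight LGAs. The weighted figures depend on which is right; the 22% does not.

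**4. What would the planned model report?** I fitted a noise-free Poisson model with period terms and a population offset, the point-estimate form of section 3.8.4. The rate ratios put in are assumptions.

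| Transition / later rate ratio | Planned estimate | Exposure from launch: equal LGAs | Exposure from launch: weighted |
|---|---|---|---|
| 1.1 / 1.0 | 1.00 | 1.04 | 1.03 |
| 1.2 / 1.0 | 1.00 | 1.08 | 1.06 |
| 1.3 / 1.0 | 1.00 | 1.11 | 1.09 |
| 1.5 / 1.0 | 1.00 | 1.19 | 1.15 |
| 1.2 / 1.05 | 1.05 | 1.11 | 1.10 |

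With a separate transition indicator the last row returns 1.20 and 1.05, the values put in.

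**5. What does the extra term cost in precision?** I took the sandwich SE of the log rate ratio under an independence Poisson GEE, without the small-sample correction. Assumptions: 2 events per 1,000 residents per period, between-LGA log-rate SD 0.1 to 0.3, cluster-period SD 0 or 0.05. Adding the indicator raises the intervention SE by about 6 to 9% with equal LGAs and 8 to 10% with the Table 1 residents (for example 0.171 to 0.189 at SD 0.2). The SEs range from about 0.08 to 0.28.

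**6. Does another analysis fill the gap?** Section 3.7.5 (time on treatment) repeats only the primary-outcome analysis and starts after the transition. No table or figure shell displays transition-period calls or presentations.

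**The case against.** The strongest reply is that the planned estimate is right for what it targets. Section 3.2 starts exposure at active implementation, and the design and sample size are consistent with that. In the last row of the table 1.05 is the correct answer for that phase, and 1.10 to 1.11 answers another question. This stands. A reader might infer that the planned rate ratio is biased, and the documents do not support that.

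Other parts also stand. No document reports a launch surge, so the sizes above are illustrations. Table 4 is a proposed timeline, and its X marks a two-month cell rather than a date, so a late launch would leave most of any surge in analysed time; 22% is therefore an upper limit. A surge lasting beyond the transition still enters the analysis. The geotargeted social media campaign ran near the end, when all LGAs had transitioned (SAP section 2.4.1), so that component is not lost. The background concern is about mass-media campaigns, and the SAP gives these outcomes no formal safety role. More chest pain calls may even be partly intended.

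It is also tempting to say that the extra indicator is free, because in the primary-outcome approximation the intervention SE hardly moves (0.0381 with the term against 0.0383 without). That does not carry over to the independence Poisson GEE planned for the rates, as step 5 shows. With SEs of that size, the data could not reliably separate 1.05 from 1.10.

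None of this removes the gap. The secondary objectives ask whether demand rises, and the plan neither analyses nor displays the launch months for that purpose.

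**Conclusion.** The point holds as a limit on what can be concluded. The planned analyses of emergency demand are valid for the active-implementation phase and leave unexamined up to 8 of 36 LGA-periods from launch onward (22%; about 27% of person-time if Table 1 residents are matched by position). Any rise confined to the launch period would go undetected, and one that fades would be understated as an effect since launch. This rests on the match between the X cells and the blank cells, since the shading of Table 4 is not visible in the text, and on launches having followed the proposed timeline. Whether a surge happened, and how large it was, is not known from the documents. The primary outcome is unaffected.

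**What to change.** Leave section 3.2 and all planned analyses unchanged. For ED presentations for unspecified chest pain, EMS calls for chest pain and EMS calls for non-chest pain, prespecify a supplementary analysis that:

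- retains the transition periods, adds a separate transition indicator, and reports its effect with a 95% confidence interval beside the intervention effect; and
- gives a second version with exposure counted from launch.

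If this is not added, limit any statement on emergency-service burden to the period after the transition.

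The cost is small. SAP section 2.5 has these outcomes collected continuously, so no new data are needed, only a few more estimates and table rows. In the supplementary rate models the intervention SE is about 6 to 10% larger under the assumptions in step 5, which is why they should sit beside the main model and not replace it.

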### 3.3 Impact of COVID-19

The original start day of the Heart Matters intervention was delayed due to the COVID-19 pandemic and associated lockdown measures. However, there were no active Government COVID-19 restrictions in the included LGAs during the trial itself; hence, no analyses are planned to account for the impacts of lockdowns.

### 3.4 Impact of flooding in rural Victoria

Between October 12 and November 30 2022, parts of Victoria were impacted by severe flooding which may have impact on the Heart Matters outcomes. Whether the effect of the Heart Matters intervention on the primary outcome was impacted by flooding will be investigated. All of the trial LGAs were impacted (<https://www.disasterassist.gov.au>) to varying degrees during this period. A model for the primary outcome will be fit as specified below, with the addition of an LGA-period level term for "impacted by flooding" and an interaction between this term and the intervention term. Estimates and 95% confidence intervals for the intervention effects for the settings of "impacted by flooding" and "not impacted by flooding", together with the p-value of the interaction term, will be reported. The "impacted by flooding" term will be 1 in all LGAs over the October and November period of the study and zero otherwise, and thus will be collinear with the corresponding term for period, which will be dropped from the model.

### 3.5 Changes from the published version of the protocol

The published protocol[1] did not include details on the analysis to assess the impact of flooding. These additions were made prior to any data being made available for analysis. Updates to the planned analysis of outcomes have been made. We have clarified that rates of non-chest pain calls to EMS during control and intervention conditions will be compared.

### 3.6 Baseline descriptions

#### 3.6.1 *Local government area characteristics*

A description of the characteristics using data from the Australian Bureau of Statistics will be presented for each LGA. These characteristics include: land size, population numbers, resident demographics (median age, proportion of males, Index of Relative Socio-economic Disadvantage and proportion born overseas).

#### 3.6.2 *Patient characteristics*

The number of patients admitted to EDs for ACS will be presented by LGA and study period. The characteristics of patients admitted to EDs for ACS will be summarised as counts and percentages (for discrete characteristics), means and standard deviations (for characteristics with approximately symmetric distributions), or medians and interquartile ranges (for characteristics with skewed distributions). Baseline characteristics will be summarised by intervention group (control vs education intervention) and by LGA and study period. Clustering will not be adjusted for in the presentation of patient characteristics. The following patient characteristics will be summarized and presented:

- Age group
- Sex at birth
- Indigenous status
- Living arrangements
- Country of birth (Australian, other English-speaking, non-English-speaking)
- Preferred language English
- Interpreter required
- ACS sub-type

The characteristics of participants responding to the Heart Watch public survey will be summarised by intervention group, data collection round and local government area. Clustering will not be adjusted for, and the following characteristics will be summarized and presented (in the manner described for patient characteristics above):

- Age group
- Sex
- Indigenous status
- Speaks another language other than English at home
- Highest level of education
- Living arrangements
- Working status
- EMS insurance
- Self-reported medical history

### 3.7 Analysis of the primary outcome

The primary outcome of arrival at hospital via EMS is a binary variable.

### **3.7.1 Main analysis**

Both a relative risk and an absolute risk difference will be estimated.

The absolute risk difference in arrival at hospital via EMS will be estimated by fitting a mixed-effects regression model with a binomial distribution and an identity link function, and random intercepts for local government areas and fixed effects for each period and for the intervention. The Kenward-Roger correction will be applied to adjust for the small number of local government areas.[16] Results will be presented as a risk difference and 95% confidence interval. In addition, an odds ratio will be estimated by fitting a marginal logistic regression model (including terms for period and the intervention) via generalized estimating equations with an independent working correlation structure with the Kauermann and Carroll correction applied to the standard errors, as recommended by Thompson et al.[17]

In the case of non-convergence of the model with an identity link, estimates will be based on the marginal logistic regression model only.

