### **SW-CRT Outcomes**

The primary and secondary clinical outcomes as listed in Table 3 will be provided to the investigators by the data sources for all Victorian LGAs over the 16-month study period and for one-year after the intervention period to examine the longer-term impact. Data for the whole of Victoria is required to enable a secondary analysis of non-study LGAs. The main primary outcome is the proportion of ACS patients that present to ED by ambulance.

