Results from the trial will be reported according to the CONSORT extension for stepped wedge cluster randomised designs. LGA and patient demographics will be described by LGA and period. All available primary and secondary outcomes will be analysed at the patient level using mixed-effects logistic regression models with a random intercept for cluster and fixed effects for each period and for the intervention. The Kenward-Roger correction will be applied to adjust for the small number of LGAs. Since there may be imbalance between the LGAs with respect to various baseline characteristics, in a secondary analysis we will adjust for potential confounders known to influence ambulance use that are available in the VEMD (e.g. age, sex, Australian born). Estimated effects will be expressed as odds ratios and as risk differences, with 95% confidence intervals. A secondary analysis will include an interaction between time and treatment to investigate a cumulative effect of the intervention over time. It has been shown that misspecification of the within-cluster correlation structure can lead to confidence intervals of incorrect widths, so sensitivity analyses allowing for more complex within-cluster correlation structures will be considered. Analyses will be conducted in Stata and/or SAS as appropriate.

We will also perform subgroup analyses (e.g. age, sex, country of birth) across the primary and secondary outcomes.

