## 2.8 Sample size

The stepped wedge design in the schematic (a six-sequence stepped wedge design, with an implementation period and two clusters assigned to the first and last sequences) will give 80% power to detect a change in the proportion of ACS patients in the eight LGAs arriving via EMS by 11%[10, 12] from a baseline of 61% to 72%, with a two-sided significance level of 5%. This detectable difference depends on an average of 40 ACS patients admitted per LGA in each two-month period (i.e. a total of 2240 ACS patients) and on the intra-cluster correlation, estimated to be 0.09 using data from the Victorian Emergency Minimum Dataset (VEMD) (2011-2015). This data indicated that more complex correlation structures, with decaying correlations over time, were unnecessary. The Stepped Wedge Stata Program was used for the sample size calculation,[13] verified using the Shiny CRT app.[14] No adjustment was made for LGA or participant attrition, as health services routinely collect the outcomes.

A sample size calculation was also conducted for two online surveys to determine a change in the level of knowledge of ACS symptoms. An online survey in 2020,[7] showed 25% of adults in the intervention LGAs (20% state-wide) could not name any heart attack symptoms. To detect a change from 25% to 10%, with 80% power and 2-sided significance level, requires a survey of 72 adults in each LGA in months 1-2 and again in months 9-10, assuming an intracluster correlation of 0.1, and a cluster autocorrelation of 0.9.

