### **3.7.5 Analysis of time-on-treatment**

To investigate whether the effect of the education campaign changed over time, the analysis in Section 3.7.1 will be repeated including separate terms for each duration of time that the intervention was implemented. Separate estimates of the effect of the intervention for each of these durations will be obtained.

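### The primary risk difference assumes a constant effect and would be badly attenuated by a gradual build-up; SAP 3.7.5 should pre-specify an exposure-averaged effect to be read beside it.

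*Supplement*

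**What the plan says.** SAP 3.7.1 fits a binomial identity-link mixed model with "random intercepts for local government areas and fixed effects for each period and for the intervention". It reports the risk difference from that model and also an odds ratio from a marginal logistic GEE with an independence working correlation. The GEE becomes the only estimate if the identity-link model does not converge. SAP 3.2 and Table 1 drop each LGA's two-month transition period.

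SAP 3.7.5 repeats 3.7.1 "including separate terms for each duration of time that the intervention was implemented". Table 8 lays out a risk difference and an odds ratio for each of 1 to 6 periods on treatment. No average of the six, no overall test, and no guidance on reading Table 8 against Table 5 is given.

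The protocol's statistical methods section states: "A secondary analysis will include an interaction between time and treatment to investigate a cumulative effect of the intervention over time". Under SW-CRT Outcomes the protocol adds: "Data for the whole of Victoria is required to enable a secondary analysis of non-study LGAs". The SAP contains no analysis of non-study LGAs.

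**The concern.** Community education delivered through coordinators, local groups and sessions may take several months to change behaviour. SAP 2.4.1 also says that a geotargeted social media campaign was added late, once all LGAs had crossed over, so delivery was not constant. In a stepped wedge, a model with one intervention term does not return a simple average of effects that vary with exposure time. LGAs that have long been exposed act partly as comparators for LGAs that cross later, so growth in their effect can be subtracted from the estimate. If that happens here, the headline risk difference could be close to zero, or negative, when the average effect over the exposed periods is as large as the trial was sized to detect. Six separate, imprecise estimates in a later table would be a weak counterweight to a single headline figure.

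**Working it through.** **Inputs.** SAP 2.8 gives "a six-sequence stepped wedge design, with an implementation period and two clusters assigned to the first and last sequences", 40 ACS patients per LGA per two-month period, ICC 0.09, 61% rising to 72%, and a two-sided 5% level. Protocol Table 4 and SAP Table 1 give launch periods T2, T2, T3, T4, T5, T6, T7, T7 over eight periods, with the launch period excluded as transition. That leaves 8 × 7 = 56 cells. Durations of 1 to 6 active periods occupy 8, 6, 5, 4, 3 and 2 cells. The other 28 cells are control cells, none of them in T7 or T8.

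**Model.** Work on cell means with total variance σ² = p(1 − p). Two cells of the same LGA have covariance ICC·σ². Each cell has variance ICC·σ² + (1 − ICC)·σ²/40. With V the resulting matrix and X holding eight period indicators and one intervention indicator, the GLS estimate is (X′V⁻¹X)⁻¹X′V⁻¹y. This is a linear approximation to the planned binomial identity-link model, with normal-theory power.

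**The plan's own figure.** N = 56 × 40 = 2240, as stated. With variance at 61%, the SE is 3.96 points and power for 11 points is 79.4%. With variance at the mean proportion, the SE is 3.83 and power 81.9%. The SAP claims that the design "will give 80% power to detect a change in the proportion of ACS patients" of 11 points, and this reproduces.

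**Weights.** Summing the intervention row of (X′V⁻¹X)⁻¹X′V⁻¹ over the cells at each duration:

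| Active periods | 1 | 2 | 3 | 4 | 5 | 6 |
|---|---|---|---|---|---|---|
| Mixed model | 0.806 | 0.403 | 0.151 | -0.029 | -0.164 | -0.167 |
| Independence estimator (linear scale) | 0.432 | 0.295 | 0.182 | 0.091 | 0 | 0 |

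The expected estimate is the sum of weight × true effect at each duration.

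**Mixed model under assumed shapes (points).**
- Linear rise averaging 11: the effects are 11·k/3.5 = 3.14, 6.29, 9.43, 12.57, 15.71, 18.86. The weighted sum is 2.53 + 2.53 + 1.43 − 0.36 − 2.57 − 3.15 = 0.4. With SE 3.96 the rejection rate is about 5.1%.
- Nothing in the first active period, then 11: 11 × (1 − 0.806) = 2.1 (equal-weight average 9.2).
- Nothing in the first two, then 11: 11 × (1 − 0.806 − 0.403) = −2.3 (average 7.3).
- Half in the first, then 11: 11 × (1 − 0.5 × 0.806) = 6.6 (average 10.1).
- Constant 11: 11.

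With cluster autocorrelation 0.9, as a block-exchangeable structure would allow, the first three become 0.6, 2.3 and −2.1. The sensitivity analysis in SAP 3.7.2 would therefore not expose the problem.

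**Independence estimator, same shapes.** It expects 6.1 (linear rise averaging 11), 6.3 (one-period delay) and 3.0 (two-period delay). It is attenuated but not reversed. Its SE on this linear scale is about 10.3 points, so it is too imprecise to settle the matter.

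**Duration-specific model.** Replacing the one indicator by six gives SEs of 4.6, 5.4, 6.3, 7.4, 9.1 and 10.5 points (variance at 61%). Their equally weighted average has SE 6.2, so the 95% CI is about ±12 points (1.96 × 6.2) and power for an 11-point average is about 43%. With variance at the mean proportion, these are 6.0 and 45%.

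**Never-treated LGAs added (assumption).** With eight more LGAs observed in all periods, the SE of the average is 3.3 points at 40 per cell and 3.9 at 15. The lowest weight in the constant-effect model is then −0.02 and −0.06 respectively. The negative weights shrink but do not vanish.

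**The case against.** Several stronger readings are tempting, and the documents do not support them.

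- *A cumulative effect would go unseen.* A reader might infer this from the near-zero headline. Table 8 is designed to show effects by duration, and a rising pattern would appear there. What is missing is a combined estimate.
- *The whole main analysis has negative weights.* Only the mixed-model risk difference does. The GEE odds ratio sits directly below it in Table 5, and a visible disagreement between the two would itself be a warning.
- *The estimate would be about zero under any build-up.* That fits a near-linear climb over all six active periods. Scaled to average 11 points, such a climb ends near 19, well above the planned effect. Other shapes tried, each reaching 11 points, gave about −4 (three-period delay) to +6.6. The model also does not assume an effect from launch, because the transition period is excluded.
- *The protocol expects accumulation.* It says only that this will be investigated, and the sample size assumes one constant change.
- *The protocol commits to non-study LGAs as never-treated controls.* It mentions a secondary analysis of those LGAs without giving them that role, and no patient volumes are given for them.

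The exposure average also has limits. It is imprecise, and it counts duration 6 (two cells, both in T8) equally with duration 1 (eight cells). A rule that a null result stands only if the average agrees would be undefined and would leave most null results unreadable.

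None of this removes the core point: the headline risk difference depends strongly on a constant-effect assumption, and no planned summary relaxes it.

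**Conclusion.** The concern holds in a limited form. Under gradual build-up the primary risk difference is badly attenuated: about 0.4 points for a linear rise averaging 11, between −2.3 and 2.1 for delays of two periods and one period, and 6.6 for a plateau by the second active period. The plan estimates duration-specific effects but never combines them into an average that could stand beside the headline. The weights rest on equal cells of 40, ICC 0.09 and a linear approximation. The effect shapes are assumptions, since the documents predict none. If the effect really is constant after transition, the planned estimate is unbiased and more precise than the average (SE about 4 against about 6 points), so 3.7.1 can remain primary.

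**What to change.** - Keep 3.7.1 as the primary analysis.
- In 3.7.5, pre-specify the equally weighted average of the six duration-specific risk differences with a 95% CI, and report it beside the primary estimate in Table 5.
- State its lower precision in advance: SE about 6 points and about 43-45% power for 11 points under the planning inputs.
- State that the constant-effect estimate will be interpreted together with this average and Table 8, without a formal agreement rule.
- Optionally, using the whole-of-Victoria data that the protocol already requests, refit both models with the other high-risk LGAs (16 listed less 8 in the trial) as never-treated controls. Label this non-randomised and secondary. The gain depends on those LGAs' patient volumes, which the documents do not give: SE of the average about 3.3 points at an assumed 40 per cell, 3.9 at 15.

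The cost is a paragraph of SAP text, one row in Table 5 and one linear combination of parameters already being fitted. The optional part adds two model fits and a comparison that randomisation does not protect.
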